**Step 1: Design the application**

In order to be able to carry out the first two techniques of the GraMI protocol (laterality recognition and motor imagery) a mobile application is required. This application will be designed by a team of UVic-UCC engineers and will be available for all devices. It will only be used by the participants in the experimental / intervention group. If, at the end of the study, the hypothesis that the GraMI protocol is effective in reducing the PLP is verified, the participants in the control group will be given the opportunity to use the application to carry out the protocol. The estimated design time for the app is four months (November 2021-February 2022), which will include piloting to test its usability and accessibility. During its design, a gamified application will be developed to encourage the motivation and adherence of the participant and aspects will be defined that will help the principal investigator in the supervision and follow-up of the intervention. In addition, the following aspects will be taken into account:

- The principal researcher of the project will install the application on the mobile device of the participant during the first educational session. This will allow you to learn how it works and help you become familiar with the application. Upon entering the application, the participant must register with their full name, username and be asked for the level of amputation (top or bottom) and side (right or left).

- The application will have two image banks differentiated according to the level of amputation (upper or lower extremity). Depending on the selection previously made by the participant, only the image bank related to his / her amputation will appear.

- Once you have entered the application, you will receive a calendar with a 6-week duration of the intervention (3 weeks for the laterality recognition phase and 3 weeks for the motor image phase).

- Through lock screens you will only be able to access the technique and level of progression that touches you at each moment of the intervention. The activity to be performed will be activated each day and the previous activity will be blocked. In this way we can guarantee the intensity and frequency established by the protocol.

- Scheduled to provide a daily reminder notification. In addition, the principal researcher of the project will contact the participant by telephone to encourage continuity with the intervention.

- The application will be designed to encourage the motivation of the participant through rankings and dynamization. The aim is to achieve greater adherence and follow-up of the intervention.

- Each attempt will be registered in the application in a database that will only have access to the research group formed by [name], [name] and [name]. The information that will be recorded will be whether or not you have completed the activity, the number of hits with respect to the total number of attempts and the speed of reaction to answer each of the images. Once the intervention is over, this data will be extracted and imported into a database that will be stored by the participant and only and will have access to the research group. The purpose of this data is to observe the follow-up carried out by the participant during the intervention, the evolution he / she has made and to observe the response time used in the laterality recognition phase.

**Step 2: RCT**

The RCT description was performed following the *Templeate for Intervention Description and Replication (TiDier)* guide 26 in order to adequately describe all aspects of the intervention and promote study replication.

The duration of the intervention, both in the control group and in the intervention group, will be 9 weeks plus 12 weeks of follow-up. The estimated start date for recruitment will be March 2022 and will run until March-April 2023.

Both the participants in the control group and the intervention group will initially receive an educational session, in person or online, on the physiology of PLP, brain plasticity and the importance of rehabilitation. It will last approximately 30 minutes where they will be explained in detail that after an amputation there is an incongruity of visual, sensitive and motor information and maladaptive plasticity due to adjacent areas occupying the areas injured by the amputation. . This educational session will be given by the principal investigator of the project, who has clinical experience, teaching and research in the field of neurorehabilitation and pain.

Control group intervention:

After the educational session, the participant will continue with the conventional treatment he / she is receiving at that time. Participants will be provided with a follow-up diary in which they will have to record their activities, specifying the nature, frequency and duration of each activity.

At the end of the study, if the hypothesis that the GraMI protocol is effective in reducing the PLP is verified, the option will be given to the participants in the control group who can perform the intervention.

Intervention / experimental group intervention:

Participants in the intervention group will receive conventional treatment plus the GraMI protocol. If they do not receive conventional treatment, they will only perform the GraMI protocol.

GraMI protocol:

Education:

At the beginning of each of the three phases, there will be an educational session of approximately 30 minutes. During each of the sessions, online or in person, the purpose of the phase in which it is located will be explained, the procedure to be followed, common objectives will be established for each phase and the normal parameters to which must be reached in the laterality recognition phase:

- Accuracy of more than 80% of accurate images.
- Average image recognition speed.

In addition, during the first educational session, the operation of the application will be explained so that the participant can become familiar and ask any questions, and notifications will also be set up to generate a daily reminder.

It is divided into three educational sessions so as not to saturate the participant with information, in this way it will be possible to strengthen the follow-up of the intervention and to resolve any doubts that may arise. These sessions will be conducted by the principal investigator.

The three phases described below do not require that the physiotherapist be always present during the operation. The participant can carry out the intervention autonomously at home, with prior training. The mobile application will record when the intervention has been carried out in order to facilitate follow-up and once a week, the principal investigator will follow up by telephone with the participant to make sure that the intervention is being carried out. . In addition, the application will include the personal email and telephone number of the researcher in order to facilitate contact at any time.

Phase 1. Laterality recognition:

The participant must observe images shown in the application, depending on the level of injury will observe images of upper or lower extremities, and differentiate with the shortest possible time if it is the right or left side of the body.

- Session intensity: 10 minutes.
- Frequency: Two sessions a day.
- Phase duration: 5 days a week for three weeks.
- Phase progression:

Day 1-5: Images in neutral positions in the different planes.

Day 6-10: Images in different positions in the different planes.

Day 11-15: Interaction with objects and functional activities.

The accuracy of the accuracy of each activity and the time used to identify each image will be recorded through the application.

Phase 2. Motor imagery:

This phase will be done through the mobile application. During the activity, images will appear, depending on the level of amputation, and the participant will have to imagine that he / she places his / her limb in the same position as the one in the image and returns it to the initial position, without perform voluntary contraction, will only perform a mental simulation, whether it is the side of the amputation or not.

- Session intensity: 10 minutes.
- Frequency: Two sessions a day.
- Phase duration: 5 days a week for three weeks.
- Phase progression (Same progression as phase 1)

Day 1-5: Images in neutral positions in the different planes.

Day 6-10: Images in different positions in the different planes.

Day 11-15: Interaction with objects and functional activities.

Each activity will also be recorded through the app. Before the start of the motor imaging phase, during the educational session, the project researcher will assess the person’s ability to imagine through the kinesthetic and visual imagination questionnaire (KVIQ) 12. It is a 10-item quiz where the physiotherapist teaches different movements and the person has to rate their ability to imagine them in the first person. In the event of a impairment of imagination, the person will be taught different strategies to do so. One of them will be before the intervention to show him/her videos and images of the affected limb in order to pre-activate the areas through the observation of the action. Another strategy is to make your imagination run wild first or try to find a factor or situation that helps you to imagine it. On the other hand, pain can occur during the imagination phase. If it appears, the person can be instructed to first imagine the movement with the healthy limb. If the pain is still triggered, we can ask you to imagine the movement in the third person. These strategies will be modified throughout the intervention to allow the person to realize the mental imagination in the first person.

Phase 3. Mirror therapy:

This phase is done with a mirror box, the mobile application is no longer used. The mirror box will be provided by the research team and once the intervention is completed, it must be returned. The participant should place the mirror in the sagittal plane between the two extremities, so that he observes the healthy end in the mirror (reflection) and the amputated end is behind the mirror. The limb behind the mirror should initially have no voluntary contraction or intentional contraction. The participant will later be asked if he or she intends to contract the stump. The size of the mirror will vary depending on the level of injury and the joints involved. If pain appears during the intervention, external factors can be sought to help tolerate the intervention (music, images ...). However, if the pain persists, it should be stopped at that time.

- Session intensity: 20 minutes
- Frequency: Once a day.
- Phase duration: 5 days a week for three weeks
- Phase progression:

Day 1-5: Analytical movements of the joints involved depending on the level of injury.

Day 6-10: Sensitive stimulation of the affected parts (textures, shapes, temperature, vibration).

Day 11-15: Interaction with functional objects and activities.

In order to follow up the intervention, the main researcher of the study will contact the participant, by telephone, once a week, in order to resolve possible doubts, clarifications or simply to remind the importance of follow-up of the intervention. In addition, the application will generate a daily notification in order to encourage continuity with the intervention.

**Step 3: Phenomenological study:**

In parallel with the RCT, as the participants in the experimental group complete the intervention, a qualitative phenomenological study will be performed. This type of study allows us to describe the experience of a person through semi-structured individual interviews(12). In addition, it allows to describe a phenomenon or an experience through the own people who suffer it (13).

Quantitative studies do not assess the experience of living with DMF and how it affects a person's quality of life. A systematic review of 2016 shows that there is little qualitative scientific evidence on a person's perception of PLP. Within the evidence we can observe studies that describe the psychological factors derived from PLP15 or the affect on the quality of life of people with amputation of the lower extremity(13). Therefore, there is a need to know the experience of people with PLP after an amputation and to identify the satisfaction obtained with the intervention.

This study will begin approximately in April 2022 and will last approximately until June 2023. During the study procedure, the qualitative study will be explained in person or by telephone to those people who are part of the intervention group. The purpose of the study and its methodology will be explained. Those who agree to participate will be sent, via email, the informed consent form and the information sheet. The appropriate number of people to participate is 15. This number is based on the scientific evidence considered appropriate taking into account the purpose of the research, the purpose of the analysis, the time and resources available(13). However, it is a forecast, it will be the saturation of data that will indicate the number of participants needed(14). Once the intervention is over, each person will be allowed to choose at what time and format (online or face-to-face) the interview was best for them. The importance of conducting the interview in person will be emphasized due to the importance of non-verbal communication between both the interviewer and the interviewee during the interview. The interview will follow a semi-structured structure based on a script but will be adapted as the interview progresses. It will consist of the following parts: demographic details, aspects related to amputation, experience of suffering from PLP and identification of the satisfaction obtained with the intervention. The approximate time for each interview will be 30-45 minutes.

The researcher conducting the interview will be an external person who has not performed the intervention or randomization, so as not to influence the questions and answers. This person has theoretical sensitivity about PLP and mirror therapy and this will make it easier to delve deeper into the topics during the interviews and better understand the experience. Subsequently, two members of the research group will perform the transcripts and analysis of the results. The aim of this triangulation is to achieve the highest possible objectivity in the results. The interviews will be recorded in voice and video format in order to be able to make a transcript as optimal as possible and will help not to lose the facial and body expressions of the participant. Only the research group and the researcher who conducted the interviews will have access to the recorded material. Each participant will have previously signed the consent to the image and voice rights. Once the study is complete, the recordings will be deleted. Once the transcripts have been completed, they will be sent to each participant to corroborate the information. This process will also be performed after the analysis of the results. You can see the consent form and the interview template in the appendices.

1. **VARIABLES:**

The assessments will be carried out by two people outside the intervention and the phenomenological study. These people will be two physiotherapists with clinical experience in the field of neurorehabilitation and / or pain, trained in research methods, calibrated with each other in order to minimize bias and will be blinded by the assignment of the groups. An initial assessment, a post-intervention assessment (9 weeks) and a follow-up assessment (12 weeks post-intervention) will be performed. The assessments will be carried out in the homes of the participants, in person and will last approximately 25-30 minutes.

The variables to be studied are differentiated between sociodemographic variables, amputation characteristics, independent variables and dependent variables. The first assessment will be the one that will last longer as all the variables will be collected, but the second and third assessment will last approximately 30 minutes as only the dependent variables will be collected.

- **Socio-demographic variables**; gender, age, marital status, height, level of education, level of physical activity, pathological and traumatic history, drugs administered and dose.

The collection of these variables will make it possible to describe the study sample and identify that the participants meet the inclusion criteria mentioned above. In this way, a sample that is as homogeneous as possible is obtained.

- **Amputation characteristics**: Cause of amputation, level of amputation, side, time since amputation, prosthetic wearer, number of hours the prosthesis is used.

- **Independent variables**: Treatment, control and intervention. All the information relevant to the conventional treatment of each of the participants will be collected.

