**Specific objectives:**

- Design a mobile application to be able to carry out the intervention and determine its usability.

- Analyze the effectiveness of the GraMI protocol in the quality of life, functionality and psychological aspects of amputated patients.

- Know the experience of the person with PLP after amputation and identify the satisfaction obtained with the intervention

1. **DESIGN**:

A RCT with a mixed methodology will be carried out, with two parallel arms and blindly simple, following the recommendations of *the Consolidate Standards of Reporting Trials - CONSORT*(11), and a phenomenological study through semi-structured interviews, following the recommendations of *the Standards for Reporting Qualitative Research*(7) which will be carried out once the intervention is over. The clinical trial was registered at ClinicalTrials.gorv (registration number: NCT05083611).

1. **SETTING:**

It will be done at the community level individually. The intervention will be carried out by the participant himself / herself and will be supervised with a follow-up by the principal researcher. The semi-structured interviews will be individual and carried out in person or by video call once the intervention is over.

1. **SIMPLE SIZE**

The sample was calculated using the G * Power program, taking into account an alpha error of 0.5, a beta error of 0.8, and an effect size of 0.81(9). In order to calculate the sample we rely on existing scientific evidence. A study11 has been selected to assess phantom limb pain using the McGill Pain Short-Form Questionnaire, and the intervention used is based on mirror neurons. The total number of participants would be 50, with 25 in each group.

1. **INCLUSION AND EXCLUSION CRITERIA:**

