The data obtained as study variables will be coded at the end of the collection, processed and analyzed by the members of the research group.

The population to be used as a sample in the analysis will include all participants who meet all the inclusion criteria, do not have any exclusion criteria and have given their consent to participate in the study. If a participant leaves before completing the study, he / she will not be replaced by another participant.

In the case of participants who have not completed the study due to dropout, have not fully completed treatment, or have even changed treatment, any data that may have been collected will be analyzed for intent to treat. The minimum number of sessions to be considered for the results will be 80%.

The program to be used for statistical analysis will be the SPSS5 program. A confidence level of 95%, and / or a statistical significance p <0.05 will be considered.

If a deviation from the intended method is considered necessary during the data analysis process, the reasons for any change will be fully documented.

To describe the sample, a descriptive statistic will be performed analyzing the mean, standard deviation, minimum, maximum and percentages of the sociodemographic variables. In addition, it will be possible to look at the average of those included and excluded in order to justify the excluded people. In this way it will be possible to describe the sample and observe the homogeneity between groups.

Next, a univariate and bivariate statistical analysis will be performed. First of all, it will be assessed whether or not the study follows a normal distribution in each of the variables. This analysis will determine whether to use parametric or non-parametric tests in the analysis of results based on the "p" value.

Equality of variance will then be analyzed through the Levenne test and finally the results will be analyzed. There will be a pre- and post-intervention analysis between groups and intragroups with a three-month follow-up. We can also analyze possible correlations between variables.

Qualitative analysis:

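### The satisfaction interviews are tied to completing GraMI, and the protocol gives no route for interviewing people who stop early or are removed

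*Protocol*

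**What the plan says.** The Specific objectives include this one: "Know the experience of the person with PLP after amputation and identify the satisfaction obtained with the intervention". The interview script in Step 3 of the Procedure has a part on satisfaction. The dependent variables and their timetable contain no satisfaction scale, so the interview is the only instrument for that half of the objective.

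On timing, the Design section describes a phenomenological study "which will be carried out once the intervention is over", and the Setting section gives the same timing. Step 3 says that the study runs in parallel with the trial, "as the participants in the experimental group complete the intervention". It then adds: "Once the intervention is over, each person will be allowed to choose at what time and format".

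On who is approached, Step 3 says that "the qualitative study will be explained in person or by telephone to those people who are part of the intervention group". This happens during the study, and taking part depends on agreement and consent.

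On numbers, Step 3 states: "The appropriate number of people to participate is 15". It calls this a forecast and lets data saturation decide the final count.

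On non-completion, the Removal criteria list two reasons for taking a participant out: a change in medication affecting pain, and a change in prosthesis use. The Quantitative analysis section foresees "participants who have not completed the study due to dropout, have not fully completed treatment, or have even changed treatment" and keeps whatever data they provided under intention to treat.

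**The concern.** GraMI is a nine-week programme done largely alone at home. The protocol treats adherence as a risk, with daily reminders, rankings and weekly telephone calls, and it acknowledges that imagery and mirror work can provoke pain. People who found the programme painful, burdensome or unhelpful are plausibly less likely to finish. If interviews happen as people complete it, selection into the sample may be related to the satisfaction being studied.

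At stake is the usefulness of the satisfaction finding. Accounts from completers alone would tend to be favourable. They would also leave out why people stop, which a clinician would want to know before offering the programme. Saturation does not protect against this: themes can saturate among completers without the views of those who left ever being heard.

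**Working it through.** This is mainly a check of the text, with one short feasibility calculation.

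**1. Is there another source for satisfaction?** No. The listed scales are the short-form McGill, EuroQol-5D-5L, FIM and Beck inventory. Anyone not interviewed contributes nothing to this part of the objective.

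**2. What do the interview statements fix?**

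| Protocol section | What it fixes | Completion required? |
|---|---|---|
| Design; Setting | Interviews follow the intervention | Not stated |
| Step 3, opening | Study runs as experimental-group participants complete | Implied by the wording |
| Step 3, invitation | Study explained to the intervention group, during the trial | No |
| Step 3, scheduling | Each person chooses time and format after the intervention | Ambiguous: could include someone whose intervention ended early |
| Removal criteria | When participants are taken out | Silent on interviews |
| Quantitative analysis | Non-completers' collected data retained | Does not cover the interviews |

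The opening of Step 3 points to completers, while its invitation sentence points to the whole arm. No section gives a route or a time for interviewing someone who stops or is removed.

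**3. Could the planned interviews come entirely from completers?** The inputs are 15 interviews (Step 3) and 25 per group (sample size section). The protocol gives no dropout rate, so the non-completion proportion d is an assumption, taken from 10% to 40%.

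- Share of the arm interviewed: 15 / 25 = 60%.
- Completers available: 25 × (1 − d).

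| Assumed d | Non-completers, 25 × d | Completers, 25 × (1 − d) |
|---|---|---|
| 10% | 2.5 | 22.5 |
| 20% | 5 | 20 |
| 30% | 7.5 | 17.5 |
| 40% | 10 | 15 |

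At every value in the range, at least 15 completers remain. Neither the target of 15 nor the saturation rule would force the inclusion of a non-completer or reveal that none had been included. This shows that a completer-only sample is compatible with the plan. It does not show that the plan specifies one.

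**4. Can the effect be sized?** No. The Qualitative analysis section plans coding into subcategories and categories by Colaizzi's method. No proportion satisfied is estimated, and the documents contain no satisfaction or dropout figures.

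**The case against.** The strongest reply is that the phrase in Step 3 describes when the study runs and does not set an eligibility rule. The invitation covers the intervention group with no completion condition and is made while the trial is under way: "During the study procedure, the qualitative study will be explained". For someone who stopped early, the intervention is also over. The consent form and interview template are in appendices not available here and may say more. This stands. A reader might infer that completion is an entry condition and that non-completers are shut out of the interviews, but the documents do not support that, because no section says so.

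A second reply is that dissatisfaction among those who leave is not established. Neither removal criterion measures it, although a medication change could follow worse pain. Pain during a session is not described as leaving the programme. This also stands: the direction of the effect is plausible but not demonstrated.

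A third reply is that purposive inclusion of non-completers is one legitimate qualitative choice among several. That is true, but it does not remove the need to say who is interviewed and when. At present, two sentences in the same step point different ways.

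**Conclusion.** The point holds as a gap in the sampling plan for the satisfaction objective. The interviews are tied to completion in one place and to the end of the intervention in others. The invitation is general, and nothing says whether or when people who stop or are removed are interviewed. Followed as written, the plan may produce a sample of completers, which would miss reasons for stopping and tend towards a favourable picture.

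The size of this cannot be quantified from the documents. A reader might want to express it as an overstated percentage satisfied, but the study does not estimate such a percentage and every input would have to be invented. The feasibility result rests on the assumed 10% to 40% non-completion and on 15 interviews being held. The tendency towards a favourable picture rests on the plausible assumption that a poorer experience makes stopping more likely.

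The primary pain comparison and the trial's sample size are unaffected. This is a cheap improvement to a secondary, qualitative objective.

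**What to change.** In Step 3 of the Procedure:

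- State that everyone allocated to GraMI is eligible for the interview, whether or not they finished.
- Offer the interview at completion or, for those who do not complete, at the point of stopping or removal.
- Seek to include some non-completers among the roughly 15 interviews.
- Report how many interviewees completed, stopped early or were removed.
- If no non-completers are interviewed, limit the satisfaction conclusion to completers.

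The timing statements in the Design and Setting sections should be aligned with this wording.

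The cost is small: the interviewer and script stay the same, and the number of interviews is about the same. Some people who stop will decline, and saturation may need a few more interviews.
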